This study, grounded in a current cross-sectional investigation employing support vector classification (SVC) algorithms, aims to explore: (1) the predictive precision of MV-FLOW^™^ endometrial vascular distribution indices and/or endometrial vascular indices for FET outcomes in RIF patients; (2) the potential of these indices to categorize patients as either successful first implantation (FI) or RIF.

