#### Ultrasound acquisition patterns and content

*2D ultrasound pattern*. In the two-dimensional grayscale mode, measurements of endometrial thickness, endometrial morphology, and endometrial motion will be conducted. Endometrial thickness will be determined by averaging three measurements of the distance between the anterior and posterior myometrium-endometrium interfaces, taken 1 cm from the endometrial apex. Detailed observation of endometrial echogenicity will be conducted, and the endometrium will be categorized into types A, B, and C based on the Gonen criteria [17]. Endometrial wave motion will be observed and documented for three minutes on the longitudinal midline section of the uterus with the probe stabilized and the patient breathing normally. Endometrial motion is classified into positive wave, negative wave, quiescent wave, bidirectional wave, local peristaltic wave according to the Ljland criteria [18].

In the two-dimensional color mode, with the uterus longitudinally bisected along its midline axis, the subendometrial region is demarcated as extending 3mm beyond the endometrial margin. Utilizing two-dimensional color Doppler flow imaging (CDFI), the perfusion of the endometrium and subendometrial areas will be assessed, classifying the flow patterns into Type I, II, and III according to the Applebaum criteria [7]. Subsequently, the CDFI is employed to delineate the uterine sagittal section, orthogonal to the long axis of the uterine cavity, where blood flow measurements are conducted. The color imaging technique is used to visualize the uterine arteries, with the sampling gate sequentially positioned at the cervix, both sides of the corpus, and the junction of the myometrium and endometrium to obtain stable blood flow spectrograms. Measurements are taken only after a minimum of consecutive stable waveforms are observed. The resultant parameters of uterine arterial blood flow encompass the peak systolic velocity (PSV), end diastolic velocity (EDV), time-averaged maximum velocity (TAMV), time-averaged peak velocity (TAPV), mean pressure gradient (PGmean), systolic/diastolic ratio (S/D), resistivity index (RI), and pulsatility index (PI).

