The MV-FlOW^™^ technology employs advanced clutter filters to evaluate low-velocity blood flow signals. To facilitate MV-FlOW^™^ sample acquisition, the sensor is positioned and the imaging adjusted to focus on the endometrium and the uterus, thereby enabling a quantitative assessment of blood perfusion. The Volumetric Index of Microvascularity (VI^MV^) is computed automatically as the ratio of blood-filled pixels to the total number of pixels within the region of Interest (ROI; VI^MV^ = n_blood/n_total). By activating MV-FlOW^™^, the operator achieves optimal visualization of the vascular tree. In this study, the ROI encompasses the entire uterus, and the VI^MV^ is determined by the proportion of endometrial blood flow pixels to the total blood flow pixels within the uterus. The parameters for the MV-Flow on the Hera-W10 system are standardized as follows: Gain at 54; Frame Average set to 8; Output Power at 90; Dynamic Range of 50; Alpha Blending at 70%; Color Map selected as 2; LumiFlow set to 2; Mechanical Index (MI) at 1.3; Thermal Index (TIs) at 0.3; and Depth calibrated to 6 cm.

*3D ultrasound pattern*. Initiating the power Doppler flow imaging mode, the sensitivity is adjusted to a heightened state to observe the branching patterns of endometrial blood flow. Subsequently, the CrystalVue^™^ mode is activated to delineate the endometrial contour, yielding a three-dimensional representation of the uterine endometrium. This process automatically calculates the endometrial volume (EV), the vascularization index (VI), the flow index (FI), and the vascular flow index (VFI).

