#### Clinical prediction model

*Machine Learning Algorithm*. In this study, the SVC algorithm was selected for machine learning applications. All computations were executed using the Sklearn package within Python 3.10.

*Data Preprocessing*. Altogether four steps of data preprocessing were applied in this study. First, we will remove the outliers and organize the data. As for missing value filling, we will conduct KNN Imputer for continuous variables, and Simple Imputer for categorical variables. The Spearman correlation analysis was first conducted to evaluate the relationship between all predictive feature variables and clinical pregnancy outcomes (Spearman’s correlation coefficient more than 0.2 were significant). Eventually, we removed low-variance (Variance Threshold = 0.8) variables and highly correlated variables (r^2^>0.8).

*Prediction Variable Selection*. Thereafter, a SVC model was constructed using the remaining feature variables. The filtered feature subset was then input into the established model to rank the feature weights. These weights indicate the contribution of each feature to the determination of the SVC hyperplane. In accordance with the LIBSVM manual, SVC_coef was employed as the feature weight to compute the permutation importance of the features, with the feature exhibiting the maximum value of the mean ± standard deviation being deemed the most valuable predictive indicator.

*Model performance evaluation*. The dataset for the predictive model was partitioned into a training set and an internal validation set in a 7:3 ratio, with internal validation of the model conducted using cross-validation techniques. The accuracy of the classification results was assessed through the use of a confusion matrix. For binary classification tasks, sample cases can be categorized into four scenarios based on their actual class and the predicted class by the trained model: true positives (TP), false positives (FP), true negatives (TN), and false negatives (FN). The model’s accuracy was evaluated using the precision ratio (P) and recall rate (R). Ultimately, the F1 score was employed to synthesize both precision and recall. Additionally, the model’s performance was evaluated using the receiver operating characteristic (ROC) curve and the area under the curve (AUC).

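### The 0.8 variance cut depends on each feature's unit and would delete VI^MV, on the 0–1 scale the article defines, before the SVC is fitted

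*Protocol article*

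**What the plan says.** Under Clinical prediction model (Data Preprocessing), the protocol article reports that "we removed low-variance (Variance Threshold = 0.8) variables and highly correlated variables". On software it says that "All computations were executed using the Sklearn package within Python 3.10".

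The same section says that "Altogether four steps of data preprocessing were applied in this study". The operations it then describes are removing outliers and organising the data, imputing missing values, a Spearman screen against clinical pregnancy, and the variance and correlation filters. Standardisation and rescaling are not among them. The SVC is built on the features that remain.

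Under Ultrasound acquisition patterns and content, VI^MV is introduced as "the ratio of blood-filled pixels to the total number of pixels within the region of Interest". For this study it is then described as the "proportion of endometrial blood flow pixels to the total blood flow pixels within the uterus".

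The Introduction gives the first aim as the predictive precision of "endometrial vascular distribution indices and/or endometrial vascular indices for FET outcomes in RIF patients". The Discussion proposes that all the uterine blood flow measures obtained by ultrasound be entered as features.

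**The concern.** A raw-variance cut means something only relative to a unit. The candidate features mix velocities, volumes, thicknesses, dimensionless ratios and categories, and one cut of 0.8 is applied to all of them. A feature on a large numerical scale passes easily. A feature on a 0–1 scale cannot pass at all. The variance filter does not look at the outcome, so predictive value plays no part in who survives.

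What is at stake is the main question. If VI^MV is stored as the fraction the article defines and the filter is run as printed, the model never sees it. The first aim could not be answered for that index through the model. A reader could also take its absence from the final feature list as evidence that it does not predict, when the cause was its unit.

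**Working it through.** **The plan's own figure.** The article gives no calculation behind the 0.8 cut, so there is nothing to reproduce there. Its one computable figure, 323 RIF patients, follows from (1.96/0.05)² × 0.30 × 0.70 = 322.7, rounded up to 323, if a margin of ±0.05 is assumed (the code is not shown). It serves below only as n.

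**Inputs.**
- Cut of 0.8, computed in scikit-learn, with no scaling step (Clinical prediction model). I take the filter to be scikit-learn's VarianceThreshold, which compares each column's variance, on the scale supplied, with the cut.
- VI^MV as a ratio or proportion (Ultrasound acquisition patterns and content). The two descriptions have different denominators, but both lie between 0 and 1, so the check does not depend on which applies.
- Training share 7:3, so 0.7 × 323 ≈ 226 RIF patients.

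**Step 1: the bound.** For a variable on [a, b], the variance is at most (b − a)²/4. For [0, 1] this is 0.25. With the n − 1 divisor the largest sample value is (161 × 162/323)/322 = 0.2508 at n = 323, and (113 × 113/226)/225 = 0.2511 at n = 226. All are below 0.8, and 0.25/0.8 = 0.31.

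**Step 2: the same in SD.** Passing needs an SD above √0.8 = 0.894. The largest possible SD on [0, 1] is √0.25 = 0.5. For an assumed VI^MV SD of 0.02 to 0.20, the variance is 0.0004 to 0.04.

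**Step 3: predictors coded 0/1.** The variance is p(1 − p): 0.0475 at a prevalence of 5%, 0.16 at 20%, 0.21 at 30% and 0.25 at 50%. None can pass.

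**Step 4: dependence on unit and scaling.**

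| Treatment of features | Consequence at a cut of 0.8 |
|---|---|
| VI^MV as a fraction, unscaled | always removed (variance ≤ 0.25) |
| VI^MV in percent, unscaled | kept if SD > 0.894 percentage points |
| All features z-scored | every variance is 1; nothing removed |
| All features scaled to 0–1 | every variance ≤ 0.25; none can pass |

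Endometrial thickness shows the same dependence. In millimetres it passes if its SD exceeds 0.894 mm; in centimetres it needs an SD above 0.894 cm, which is 8.94 mm.

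**Step 5: software check.** VarianceThreshold(0.8) was run on simulated columns of length 323. It dropped a skewed 0–1 ratio (variance 0.022), a uniform 0–1 column (0.083), an RI-like column (0.003) and a 0/1 column (0.250). It kept a ratio drawn from the same skewed distribution but expressed in percent (variance 236). After standardisation it kept every column. This confirms how the filter behaves; the conclusion rests on the bound.

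**The case against.** The strongest reply is that deletion depends on a recording unit the article does not fix. VI^MV is said to be computed automatically, and the ratio is given as a definition, not as an export format. The system might store 12 where the definition implies 0.12. Unspecified data organisation might also include standardisation, and an article may leave that to the full plan. Either route would in practice keep VI^MV in the model. This stands as a limit on certainty. It does not clear the rule: the article prints the threshold, the software, a count of steps and the definition of the index, and taken together they remove the index.

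A second reply is that 0.8 was shorthand for the Bernoulli rule, 0.8 × (1 − 0.8) = 0.16. That is not what is written. Under it, yes/no predictors with prevalence between 20% and 80% would survive, but a 0–1 ratio would still need an SD above √0.16 = 0.40, and even a uniform 0–1 variable has only 0.289.

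Several stronger readings are tempting, and the documents do not support them:

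- *That MV-FLOW certainly cannot enter the model.* This holds only for an unscaled 0–1 column. The first aim also refers to vascular distribution indices, and no scale is given for a separate index of that kind, so loss of every MV-FLOW measure is not shown. The Spearman analysis, which is described before the filter, and the group comparisons under Data statistics do not depend on the cut.
- *That RI and every yes/no predictor must go.* The article gives no formula for RI. It is bounded by 0 and 1 under the usual definition with non-negative end-diastolic velocity. No coding is stated for categorical variables either. A −1/+1 variable has variance 4p(1 − p), or 0.84 at 30% prevalence, and five equally frequent integer-coded levels have variance 2.0.
- *That scaling makes no difference.* Z-scoring would keep VI^MV; the filter would then be redundant, not harmful. With all features scaled to 0–1, scikit-learn stops with an error when no feature passes, so the analyst would notice. Silent loss arises with unscaled features in mixed units.

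**Conclusion.** The rule is wrong as written and should be corrected before the model is built. On the 0–1 scale that the article itself defines, with no scaling step, VI^MV has a variance of at most 0.25 against a cut of 0.8 and is deleted in every possible data set. The same holds for any predictor coded 0/1, and for RI if it is bounded by 0 and 1. This contradicts the first aim in the Introduction and the Discussion's proposal to enter all the flow measures.

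The conclusion assumes that the filter is scikit-learn's raw-variance filter, that VI^MV is stored as a fraction, and that no unstated scaling comes first. If VI^MV is stored in percent or the features are z-scored, the deletion need not occur. The defect is then that the rule's effect depends on an unstated unit, or that the rule does nothing.

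**What to change.** Delete the 0.8 variance cut, or replace it with a unit-free near-constant rule, for example dropping a feature only if almost all patients share one value. State the unit or scaling of every feature, including whether VI^MV is a fraction or a percentage, and state how categorical variables are coded. Add that no variance filter may remove the MV-FLOW indices.

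This point does not call for exempting MV-FLOW from the Spearman or collinearity screens. Neither is faulted here, and forced entry would be a separate modelling choice.

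The cost is a few sentences under Data Preprocessing and no additional data. The downside is that a few more features stay in the model.

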#### Sample size calculation

This study is a cross-sectional trial to establish a predictive model for endometrial receptivity and pregnancy outcomes using SVC to predict clinical pregnancy. The ultrasound assessments of uterine arteries and endometrial thickness are crucial for pre-implantation evaluation of endometrial receptivity, a study involving 78 FET patients (resulting in 45 clinical pregnancies, 57.7%) utilized elastic ultrasound imaging and nine predictive indicators based on basic information, achieving a predictive accuracy of 76.92% [15]. Sample size estimation was conducted using “pmsampsize” in R software [16]. According to the definition of RIF, at least two failed ETs were diagnosed as RIF. Assuming a clinical pregnancy rate of 30%, a minimum of 323 RIF patients were required for sample estimation. In a 1:1 ratio, 323 FI patients were also included. The code for sample size calculation is referenced in S1 Fig.

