However, most prior studies have relied on retrospective analysis, potentially yielding biased results. Hence, prospective research remains essential to evaluate the feasibility and precision of ultrasound-derived uterine blood flow parameters in predicting the optimal embryo transfer timing in IVF. This protocol outlines a prospective, cross-sectional study that explores the role of ultrasound in pre-embryo transfer diagnostics. Building on this, we have pioneered the use of MV-FLOW^™^ to detect microvascular distribution within the endometrium and sub-endometrium, and validated its feasibility in assessing endometrial vasculature [11]. SVC [25] is a common supervised machine learning algorithm that seeks an optimal hyperplane in feature space to discriminate between different classes, characterized by excellent generalization capabilities. We propose to input all ultrasound-derived uterine blood flow parameters as flow features to predict embryo implantation outcomes and rates, thereby identifying the most predictive ultrasound indices for embryo implantation and discussing the diagnostic value of MV-FLOW^™^ in assessing endometrial receptivity. RIF is predominantly influenced by embryonic or uterine factors, with studies indicating abnormal blood flow parameters [26]. Our study extends this by investigating the clinical utility of these parameters in differentiating between successful first-time transfers and RIF cases, offering predictive markers for RIF identification.

In conclusion, while we have discussed the potential effects of MV-FLOW^™^ in predicting frozen embryo transfer outcomes in patients with recurrent implantation failure, it is important to consider the broader clinical implications should our study’s predictions prove accurate. Successful prediction models could revolutionize personalized treatment plans, allowing clinicians to tailor interventions more effectively and improve overall success rates in assisted reproductive technologies. This could lead to a paradigm shift in how recurrent implantation failure is managed, ultimately enhancing patient outcomes and satisfaction. Furthermore, the integration of MV-FLOW^™^ with multidimensional ultrasound features could pave the way for more comprehensive diagnostic tools, offering deeper insights into the underlying causes of implantation failure and facilitating more targeted therapeutic strategies.

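### Single-feature ranks are not comparable between families of correlated Doppler indices and a single MV-FLOW index, so the planned ranking cannot by itself support a comparison of MV-FLOW with conventional Doppler

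*Protocol article*

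**What the plan says.** In the Protocol article, under Clinical prediction model, an SVC is fitted to the features left after preprocessing, and these are ranked by weight. The text states: "These weights indicate the contribution of each feature to the determination of the SVC hyperplane". The coefficients are then used to obtain permutation importance, and the single feature with the largest value is declared the most valuable predictor.

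Preprocessing includes a Spearman correlation with clinical pregnancy (cut-off 0.2), after which the investigators "removed low-variance (Variance Threshold = 0.8) variables and highly correlated variables", the latter at r² above 0.8. The text does not say which member of a correlated pair stays.

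The features are described under Ultrasound acquisition patterns and content:
- **Uterine artery:** eight indices (PSV, EDV, TAMV, TAPV, PGmean, S/D, RI, PI), "with the sampling gate sequentially positioned at the cervix, both sides of the corpus, and the junction of the myometrium and endometrium".
- **3D power Doppler:** VI, FI and VFI, plus endometrial volume.
- **MV-FLOW:** one named index, VI^MV. The aims in the Introduction speak of MV-FLOW indices in the plural.

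The Discussion says that the model serves for "identifying the most predictive ultrasound indices for embryo implantation" and, from there, for discussing the diagnostic value of MV-FLOW.

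**The concern.** Indices derived from one arterial waveform can stand in for one another. A linear SVC spreads its weight over them. Permuting one of them costs little, because the others still carry the signal. A low value for each arterial index is therefore compatible with a large contribution from arterial flow as a whole. An index without close relatives keeps all of its own credit. Standardising the features or using true permutation importance does not change this.

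The ranking is the stated route to naming the best ultrasound index and to the conclusion on MV-FLOW. If VI^MV came out on top, the paper could present it as more informative than conventional Doppler when conventional Doppler, taken together, carried more. If VI^MV came out low, that too would be hard to interpret.

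**Working it through.** **1. The plan's own figure.** The Sample size calculation section says: "Assuming a clinical pregnancy rate of 30%, a minimum of 323 RIF patients were required for sample estimation". The criterion for estimating the overall outcome proportion, with an assumed margin of 0.05, gives (1.96/0.05)² × 0.30 × 0.70 = 1536.64 × 0.21 = 322.7, rounded up to 323. This reproduces the figure, and the present point does not affect it. It implies 323 × 0.30 ≈ 97 pregnancies, and the 7:3 split gives 226 and 97 women.

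**2. What the correlation filter lets through.** r² > 0.8 means |r| > √0.8 = 0.894. Strongly related indices below that stay in together.

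**3. Simulation model.** The documents give no effect sizes or correlations, so these are assumptions. F is the latent arterial signal and M the latent MV-FLOW signal.
- Family index j = √r·F + √(1−r)·error, for j = 1 to k, so pairwise correlation is r.
- VI^MV = √r·M + √(1−r)·error.
- Log-odds of pregnancy = a + b_F·F + b_M·M, with about 30% events and n = 323.
- The SVC is linear, on standardised features. Importance is the AUC lost on permuting a column, or all columns of the family together.

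**4. Equal signal** (b_F = b_M = 0.6, F and M independent, 200 runs per row, importance computed on the fitted data):

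| k, r | Mean loss per family index | Loss for VI^MV | Loss for family as a block | VI^MV ranked first | VI^MV above the block |
|---|---|---|---|---|---|
| 1, 0.8 | 0.096 | 0.097 | 0.097 | 52% | 51% |
| 3, 0.8 | 0.031 | 0.095 | 0.114 | 66% | 40% |
| 8, 0.6 | 0.014 | 0.067 | 0.142 | 65% | 12% |
| 8, 0.8 | 0.022 | 0.085 | 0.135 | 53% | 21% |
| 8, 0.88 | 0.028 | 0.094 | 0.137 | 41% | 20% |

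Within each row the family indices and VI^MV have nearly the same AUC when used singly (0.61 to 0.64), yet each family index is credited with a third or less of what VI^MV gets once k is 3 or more. The last row has r² = 0.77 and passes the filter.

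**5. Arterial effect 1.5 times that of VI^MV** (r = 0.7, no Spearman screen; four simulations with separately written code):

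| Simulation | VI^MV first, one arterial index | VI^MV first, eight | Family block beats VI^MV |
|---|---|---|---|
| A | 23% | 33% | 88% |
| B | 15% | 39% | 93% |
| C | 19% | 38% | not computed |
| D | 13% | 42% | 93% |

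In A, mean AUC losses are 0.017 per arterial index, 0.055 for VI^MV and 0.145 for the family. In B they are 0.016, 0.053 and 0.165. At twice the effect, VI^MV still ranks first in 28% of runs in B, while the family block wins every one of 300 runs.

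**6. Where the direction changes.**
- **VI^MV with no signal of its own** (latent correlation 0.7 with the family, k = 8, r = 0.8): first in 2-3% of runs. With a small own effect (0.3): 10-12%.
- **Very high correlation within the family:** at k = 8, r = 0.88, first place is 41% with equal signal and 12% with a weaker VI^MV (0.4 against 0.6). One family index gives 52% and 17% (run at r = 0.8).
- **Spearman cut of 0.2 used for selection,** in the setting of step 5: VI^MV survives in 36-38% of runs, while about 7.5 of the 8 arterial indices survive.
- **Variance filter:** a quantity between 0 and 1 has variance of at most 0.25, below 0.8. VI^MV held as an unscaled fraction would be removed; as a percentage it may stay.

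**The case against.** **The quoted sentence is not false on its face.** The coefficients of a linear SVC do define the hyperplane. This stands for the sentence alone. It does not cover the next step, where the largest value is read as the most valuable predictor of pregnancy.

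**The plan looks for a single indicator, not a modality.** This is fair, and it is why the single-index ranking should stay. But the Discussion carries the ranking over to the value of MV-FLOW as a technique, and that is a question about modalities.

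**A reader might infer that the plan favours MV-FLOW.** The documents do not support that. It requires a single MV-FLOW index with a signal of its own, little overlap with the 3D vascularization index, and survival of both the variance filter and, if used for selection, the Spearman screen. The Introduction speaks of several MV-FLOW indices, and the acquisition section describes VI^MV in two ways.

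**A reader might also blame the r² filter for deleting the competitors.** If one member of a correlated pair survives, it gathers the family's credit, and with equal signal the ranking is even (52%). Reading the text as deleting both members is strained. What remains is that the retained member is unnamed and that VI^MV could be the one dropped.

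**Comparing VI^MV with the average arterial index gives a more striking number** (VI^MV ahead in 85% of runs in the setting of step 5). The plan's rule concerns the maximum, so first place is the relevant measure. By that measure an arterial index still wins in most runs of that setting.

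**Grouped importance has its own tilt.** Eight readings measure a signal more accurately than one, and a larger block can also gain from overfitting if importance is computed on the fitted data. This stands, so the grouped measure belongs on validation data.

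**Conclusion.** The point holds as one of comparability. The plan ranks single features where conventional Doppler enters as families of correlated indices and one MV-FLOW index is named. Importance is split within a family, and the r² > 0.8 cut does not prevent this. The ranking therefore cannot establish where MV-FLOW stands against conventional Doppler, in either direction.

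As to size: with an arterial effect 1.5 times larger, VI^MV's share of first places rises from 13-23% with one arterial index to 33-42% with eight, although the arterial family as a block beats it in 88-93% of runs. This rests on assumed effects, equal correlations within the family, equal reliability, standardised features and no Spearman screen. Overlap of the latent signals of 0.3 or 0.5 leaves first place at about 40%. Lack of an own signal for VI^MV, or either of the other two filters, can remove the shift. This is a cheap improvement to a stated rule, and it casts no doubt on the data collection or the sample size.

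**What to change.** In the Clinical prediction model section:
1. Keep the single-index ranking, labelled descriptive, and state that weights of correlated indices are shared and are not separate contributions.
2. Define the index families before analysis: uterine-artery Doppler over all sites, 3D power Doppler, CDFI type, grayscale features, and MV-FLOW with all its indices.
3. Base any statement about MV-FLOW against conventional Doppler on grouped permutation importance, permuting all columns of a family together on validation data, or on the validated AUC of the model with and without MV-FLOW. Give an interval: the 97 held-out women contain only about 97 × 0.30 ≈ 29 pregnancies.
4. For pairs above r² = 0.8, keep one member named in advance.

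The cost is a few lines of text and code, with no new data and no change to recruitment. The downside is that the comparative conclusion is about families, and single indices within a family are only described.
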